The few TMS or TBS studies using a crossover design (Eggers et al., 2010; Maruo et al., 2013; Bologna et al., 2015; Kim et al., 2015; Vanbellingen et al., 2016; Yokoe et al., 2018; Hill et al., 2020; Brugger et al., 2021) have demonstrated the favorable efficacy of high-frequency rTMS over the M1 on motor symptoms in PD (compared to sham stimulation). The necessary sample size was calculated based on the primary endpoint, i.e., the motor clinical changes as assessed by the UPDRS-III score. Considering these findings and the statistical parameters needed to detect a treatment difference for a 2 × 2 crossover study at a two-tailed *p* value of 0.05 and a power of 80%, the total sample size was calculated to be at least 21 subjects. With an assumed drop-out rate of approximately 20%, we estimated a final minimum sample size of 24 patients.

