### Outcome measures

Participants will undergo an extensive assessment of seven areas of interest: basic demographic information, clinical and motor assessment, TMS-EMG parameters of cortical excitability, cognitive and neuropsychiatric evaluations, electrophysiology and neuroimaging examination, and serum biomarker testing. Each measure will be collected before and after treatment for both the real and sham groups and during the two phases of the study. Primary, secondary, and exploratory outcome measures are summarized in the Table 1.

**Table 1 tab1:** Primary, secondary, and exploratory outcome measures.

	Measure	Domain measured

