### Data collection and analysis

Figure 1 provides a visualization of the complete experimental design including the two phases as well as the washout period and crossover process. Recruitment will be managed by three experienced neurologists who, based on patients’ clinical reports and interviews, will determine their suitability for participation in this investigation. Phase I and Phase II will be identical but differ in terms of groups (i.e., patients who received real iTBS will subsequently receive sham iTBS and vice versa). Patients will be randomly assigned to two equal groups (real or sham) in blocks. Data collection and iTBS sessions will not be performed by the same person to ensure blinding. The full protocol and data acquisition will be performed at the Puerta del Mar University Hospital.

Figure 2 provides a summary of the approximate schedule of patient data acquisition in both phases. Once data are collected, we will determine differences in all outcome parameters before and after intervention and between the real and sham stimulation groups.

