### Statistical analysis

Before any statistical analyses are performed, the normality of the data distributions of outcome variables and parameters will be assessed using the Shapiro–Wilk test to determine whether parametric or nonparametric statistical tests should be used for the different measures in this study. Subjects will act as their own controls, and the data will be analyzed using both parametric (independent-samples *t*-test) and nonparametric (Mann–Whitney U test) methods, as appropriate. To evaluate the carryover effects, a preliminary test will be performed to test the assumption that the washout phase lasted long enough to completely eliminate a carryover impact. To do this, an independent-samples test will be used to compare the sum of the values measured in the two periods for each subject across the two sequence groups.

In the first step, exploratory analysis of correlations between the clinical response variables and all outcome measures will be conducted. Primarily, correlation analyses will be applied to examine correlations of TMS-EMG parameters with motor, clinical, and neurocognitive variables as well as serum biomarkers and brain structural and functional variables. In a second step, significant correlations across timepoints (i.e., use of baseline variables to predict the clinical response at posttreatment) will be analyzed using stepwise multiple regression models to identify the potential factors predicting the clinical response after iTBS.

For structural MRI and functional (EEG, fMRI) data, individual analysis will first involve the statistical pipeline of each software or toolbox (e.g., SPM12, Fieldtrip, Brainstorm, etc.). Next, advanced statistical analysis will be performed by incorporating clinical, cognitive, neuropsychiatric, serum biomarker, electrophysiological, and neuroimaging information using SPSS 23.0 (IBM, Chicago, IL, United States), R, and custom routines written in MATLAB (MathWorks, Natick, United States). Issues affecting the risk of bias related to missing data in our crossover study will be considered. Initially, all patients with missing outcome data will be removed from the analysis of each data subset. Other strategies for managing missing data, such as the last observation carried forward, will also be used to impute values. The threshold for statistical significance will initially be set at *p* < 0.05. All statistical tests will be two-tailed and adjusted for multiple comparisons.

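### The motor score has a new baseline in each phase, but the named tests cannot adjust for it; at an assumed correlation of 0.5 this costs about 8 points of power

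*Protocol article*

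**What the plan says.** The Procedure and intervention section gives each phase its own baseline evaluation, including a motor examination. The Outcome measures section confirms this for the whole battery: "Each measure will be collected before and after treatment for both the real and sham groups and during the two phases of the study". The legend to Figure 2 applies the same timeline to both phases.

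Under Recruitment and sample size, the primary endpoint is "the motor clinical changes as assessed by the UPDRS-III score". Data collection and analysis describes the comparison: "we will determine differences in all outcome parameters before and after intervention and between the real and sham stimulation groups".

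The Statistical analysis section names the tests: "Subjects will act as their own controls, and the data will be analyzed using both parametric (independent-samples *t*-test) and nonparametric (Mann–Whitney U test) methods". It adds a preliminary carryover test that compares within-patient sums between the two sequences. Baseline variables enter a model in one place only, the stepwise regression that looks for predictors of response. That is not the real-versus-sham comparison.

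**The concern.** Neither an independent-samples t-test nor a Mann–Whitney test can use a covariate. The phase baseline is therefore either subtracted, if changes are compared, or ignored, if post-treatment scores are compared. Subtraction fixes its slope at 1; ignoring it fixes the slope at 0.

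This is separate from pairing and phase effects. Suppose the test is run in the correct crossover form, comparing Phase I minus Phase II differences between the two sequences. Each patient's stable level then already cancels between phases. Only phase-specific fluctuation still links baseline to follow-up, and with equal variances the efficient slope is ρ, which is below 1. When ρ is below 0.5, subtracting the phase baseline adds more noise than it removes.

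Nothing is biased. What is at stake is precision in a small trial: "the total sample size was calculated to be at least 21 subjects". A real motor benefit is more likely to be missed than the collected data require.

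**Working it through.** **Inputs from the protocol** (Recruitment and sample size): two-sided α = 0.05, power 80%, 21 evaluable patients, 24 enrolled, 2 × 2 crossover. No effect size, standard deviation or correlation is given, so the figure of 21 cannot be reproduced. The stated 80% at 21 is used as the anchor instead.

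**Assumption.** For each patient let D_B be the Phase I minus Phase II difference in baseline and D_Y the same difference in post-treatment score. They have equal variance σ² and correlation ρ within sequence. ρ is not the ordinary baseline-to-follow-up correlation. If that is r_w within a phase and every cross-phase correlation is r_b, then ρ = (r_w − r_b)/(1 − r_b). For example, r_w = 0.8 and r_b = 0.6 give 0.2/0.4 = 0.5.

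**Variances**
- Change score: Var(D_Y − D_B) = 2(1 − ρ)σ²
- Post score: Var(D_Y) = σ²
- Baseline-adjusted: (1 − ρ²)σ²

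Adjusted over change is (1 − ρ²)/[2(1 − ρ)] = (1 + ρ)/2. Adjusted over post is 1 − ρ². At ρ = 0.5 both are 0.75.

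**Anchor.** With 21 patients and 19 degrees of freedom, 80% power needs a noncentrality of 2.954, a standardised effect of 2.954/√21 = 0.6445. With 24 patients the noncentrality is 0.6445 × √24 = 3.158, and power is 85.5%.

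**Adjusted analysis.** Divide the noncentrality by √[variance ratio × (1 + 1/(N − 4))], where the second factor is the price of estimating the slope, and use N − 3 degrees of freedom.
- N = 21, ρ = 0.5: 2.954/√(0.75 × 1.0588) = 3.314 on 18 df, power 88.0%.
- N = 24, ρ = 0.5: 3.158/√(0.75 × 1.05) = 3.558 on 21 df, power 92.4%.

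**Range at N = 21**, with the unadjusted test set to 80% in each column:

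| ρ | Adjusted power if plan uses change | Adjusted power if plan uses post score |
|---|---|---|
| 0 | 97.0% | 77.5% |
| 0.2 | 93.8% | 79.1% |
| 0.3 | 92.0% | 81.2% |
| 0.5 | 88.0% | 88.0% |
| 0.6 | 85.9% | 92.4% |
| 0.7 | 83.7% | 96.7% |
| 0.8 | 81.6% | 99.5% |
| 0.9 | 79.5% | above 99.9% |

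The gain is 5 points or more for ρ up to about 0.6 if changes are compared, and from ρ of about 0.45 if post scores are. The worst losses are 0.5 points (change, ρ = 0.9) and 2.5 points (post score, ρ = 0).

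**Simulation check** (40,000 crossovers per setting, N = 21, change score against adjusted): 80.0% and 87.8% at ρ = 0.5; 80.1% and 91.8% at 0.3; 80.0% and 83.6% at 0.7.

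**Slack.** The protocol states: "With an assumed drop-out rate of approximately 20%, we estimated a final minimum sample size of 24 patients". Losing 20% of 24 leaves 24 × 0.8 = 19.2, about 19 patients. On the same anchor, power is then 75.4% unadjusted and 83.8% adjusted at ρ = 0.5.

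**The case against.** The strongest reply is that this is a refinement and not an error. Comparing the sequences on within-patient phase differences with a two-sample test is a standard, valid crossover analysis, and covariates are often left to a statistical analysis plan. That it is valid stands. But the section does not leave the method open. It names the tests, the rule for choosing between them and the carryover procedure, and the named tests exclude the covariate.

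Second, the size rests on an assumed ρ and on the outcome analysed. The Statistical analysis section does not itself say change or post score; change is read from the endpoint and from Data collection and analysis. At ρ = 0.5 the two readings agree, but away from it one of them gains less than 8 points, and a low ρ with post scores gains nothing. The 80% is also borrowed, because the protocol does not say which analysis it belongs to. All of this stands, so the 8 points must be read with the table.

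Third, the Phase II baseline follows Phase I treatment. If an effect persists through the washout, that baseline depends on sequence, and adjustment then moves the estimate. This is a real caveat, chiefly against an unadjusted post-score analysis. A change score carries the same contamination at full weight, the adjusted analysis only at slope ρ.

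Fourth, the protocol schedules four post-treatment motor evaluations and a nonparametric fallback, and the adjusted analysis must settle both. So must the planned one.

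**Conclusion.** The concern holds. The plan collects a motor baseline in each phase and fixes a primary comparison that cannot adjust for it. With 21 patients and 80% power for the planned test, the cost is about 8 points at ρ = 0.5 (about 7 points with all 24 patients). That rests on equal variances, on the assumed ρ, on a baseline that does not depend on sequence, and on the stated power applying to the named test. Over most plausible values the adjusted analysis gains; where it does not, it loses at most about 2.5 points. The planned analysis is unbiased in this respect, so this is an improvement that should be made, not a fatal flaw. Confidence in its size is moderate because the protocol gives no correlation.

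**What to change.** In the Statistical analysis section, state the primary MDS-UPDRS-III analysis as a baseline-adjusted crossover analysis. For each patient, take the Phase I minus Phase II difference in the post-treatment score at a named visit. Regress it on sequence (real first or sham first), with the Phase I minus Phase II difference in baseline score as covariate. The treatment effect is half the sequence contrast.

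A mixed model with patient, phase and treatment is an equivalent form, provided it enters the within-patient part of the phase baseline, so that differences between patients do not distort the slope. Use the same form for the other outcomes that have a baseline in each phase. Say what replaces it if the normality check fails, and acknowledge that it assumes no residual Phase I effect in the Phase II baseline.

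The change is to wording only, with no new patients, visits or measurements. It uses one degree of freedom (18 in place of 19 with 21 patients). It should be fixed before any unblinded analysis.

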### Recruitment and sample size

The recruitment period will last approximately one and a half years. During this time, we plan to enroll 24 PD patients who meet the inclusion and exclusion criteria. Recruitment will be entirely managed by neurologists from the Movement Disorders Unit at the Puerta del Mar University Hospital. Every candidate patient will undergo a clinical review by a neurologist specializing in movement disorders, who will assess the suitability of each patient for inclusion in this study.

The inclusion criteria for patients will be as follows: (i) diagnosed with PD according to the United Kingdom Parkinson’s Disease Society Brain Bank diagnostic criteria (UK PDSBB; Gibb and Lees, 1988); (ii) disease duration of at least 5 years to reduce the risk of including levodopa-responsive atypical Parkinsonism patients (Lang et al., 2006; Tolosa et al., 2006; Mestre et al., 2014); (iii) disease symptomatology in the ON medication state at a Hoehn y Yahr (H&Y) scale of II–III; (iv) clinical and therapeutic stability in the last 2 months previous to the recruitment period; and (v) aged 45–75 years.

The exclusion criteria will be as follows: (i) lack of a PD diagnosis that meets the UK PDSBB diagnostic criteria; (ii) presence of a serious systemic disease; (iii) presence of severe or moderate cognitive impairment comparable to dementia as indicated by a Mini-Mental Parkinson (MMP) score of ≤24; (iv) any incapacitating psychiatric or other clinical condition that might affect the correct performance of this protocol, such as any dystonia and/or dyskinesia; (v) receipt of amantadine within the previous 60 days; and (vi) any sign of atypical parkinsonism, neurological comorbidities, or history of cranioencephalic traumatism or epilepsy or any other contraindication to neurostimulation with TMS (e.g., magnetic intracranial implant, cardiac pacemaker).

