Thus, by identifying potential electrophysiological, neuroimaging and serum markers underpinning iTBS-induced dopamine-dependent corticostriatal plasticity, our study could pinpoint the ideal biomarkers responsible for short- and long-lasting effects on motor function in PD, offering these patients an optimized adjunct to dopamine replacement therapies.

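### Predictors of response are chosen by correlation screening and then stepwise regression in the same 21 to 24 patients, so the reported fit and p-values will be optimistic whichever way the multiplicity rule is read

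*Protocol article*

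**What the plan says.** The Statistical analysis section sets out two steps. First, "exploratory analysis of correlations between the clinical response variables and all outcome measures will be conducted". Second, "significant correlations across timepoints (i.e., use of baseline variables to predict the clinical response at posttreatment) will be analyzed using stepwise multiple regression models", with the aim of finding factors that may predict response after iTBS. It gives no candidate list, no cap on model size and no internal validation.

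On error control, the section says "The threshold for statistical significance will initially be set at *p* < 0.05" and then that every test will be two-tailed and adjusted for multiple comparisons. The adjustment method and the family of tests are not named.

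Clinical response is not defined: the text does not say whether it is the result in the real-stimulation phase, a change from baseline, or the difference between a patient's real and sham phases.

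On numbers, under Recruitment and sample size, "we plan to enroll 24 PD patients who meet the inclusion and exclusion criteria", and "the total sample size was calculated to be at least 21 subjects". The Discussion says that "our study could pinpoint the ideal biomarkers responsible for short- and long-lasting effects on motor function in PD".

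**The concern.** Three features combine badly.

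- **Many candidates, few patients.** The candidates outnumber the patients by more than two to one before imaging is counted.
- **The same data used twice.** Variables enter the regression because they correlated with the response in these patients, and the model is then fitted and tested in them. Standard p-values and R-squared assume that the model was fixed in advance.
- **An unclear target.** If response means the outcome of the real phase alone, a baseline variable that predicts sham response, natural fluctuation or regression to the mean cannot be told apart from one that predicts benefit from iTBS.

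The primary efficacy comparison is not affected. At stake is the biomarker aim, to which the Discussion gives considerable weight: a model with good apparent fit could be reported when nothing predicts response.

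**Working it through.** The article gives no figure for this analysis, so there is none to reproduce. The check counts candidates and works out what the procedure yields when no candidate is related to response.

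**Candidate count (Table 1 and the Methods sections on each measure)**

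| Group | Count |
|---|---|
| MDS-UPDRS II, III, IV | 3 |
| LEDD, PFS-16, PDQ-39 | 3 |
| MMP, FAB, BVRT | 3 |
| Neuropsychiatric scales | 8 |
| TMS-EMG: (3 thresholds + 3 from the 20 t recording + 5 from the cSP) × 2 hemispheres | 22 |
| EEG: 8 bands × 2 eye conditions | 16 |
| NfL, GFAP, BDNF | 3 |
| **Total** | **58** |

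Regional grey matter volumes, cortical thickness, functional connectivity, graph metrics, single electrodes and subscales would all add to this.

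**Reading A: the screen is not adjusted (p < 0.05)**

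- Expected false correlations: 58 × 0.05 = 2.9.
- Chance of at least one, independent predictors: 1 − 0.95^58 = 94.9%.
- Correlated predictors were simulated under the null: 58 predictors, screen at p < 0.05, then stepwise with entry 0.05 and removal 0.10 (assumed, since the article gives no criteria).

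| Correlation between predictors | Noise model, n = 24 | Noise model, n = 21 | Median apparent R², n = 24 / 21 |
|---|---|---|---|
| 0 | 95% | 94% | 0.39 / 0.43 |
| 0.3 within groups | 91% | 91% | 0.34 / 0.36 |
| 0.5 within groups | 85% | 86% | 0.28 / 0.32 |
| 0.7 within groups | 76% | 76% | 0.26 / 0.29 |

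If all 58 predictors share one common correlation, rather than correlating only within groups, the chance at n = 24 is 83% at 0.3 and 67% at 0.5. Mean apparent R-squared across these settings runs from about 0.27 to 0.42; the true value is 0.

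These figures are per response variable. With three response variables (assumed correlation 0.6) and within-group correlation 0.5, the chance of at least one false screening result is 99%. With twelve (three MDS-UPDRS parts × four post-treatment motor evaluations) it is close to 100%.

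**Reading B: the screen is adjusted over the 58 tests**

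- Bonferroni level: 0.05 / 58 = 0.00086. Chance of any false predictor, independent tests: 1 − (1 − 0.05/58)^58 = 4.9%. Simulated: about 3% to 5% with Bonferroni, 4% to 5% with Benjamini-Hochberg.
- Smallest correlation that passes, from r = t / √(n − 2 + t²). At n = 24, t = 3.853, so r = 3.853 / √(22 + 14.85) = 0.635. At n = 21, t = 3.948, so r = 3.948 / √(19 + 15.59) = 0.67.
- Any variable that passes therefore has an apparent R-squared of at least 0.635² = 0.40 (n = 24) or 0.67² = 0.45 (n = 21). A noise model that gets through shows on average about 0.45 to 0.52.
- Real associations are exaggerated too. At n = 24, a true correlation of 0.4 passes 7% of the time and then averages 0.69; a true 0.5 passes 19% of the time and then averages 0.70.

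**The response variable.** Write a patient's real-phase response as a background part (sham response, fluctuation, regression to the mean) plus the iTBS effect. A predictor of the background part correlates with the real-phase response even if the iTBS effect is identical in everyone. In the real-minus-sham difference, the background part common to both phases cancels.

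**The case against.** **Adjustment is promised.** A reader might infer that a false predictive biomarker is almost certain. The document does not support that. The same section says that all tests are adjusted; if this covers the screen, the chance of a false predictor is about 3% to 5%. Even unadjusted, for one response variable it can be as low as 67% to 76% when predictors are strongly correlated. That is plausible here, since the two cSP ratios are computed from other listed measures. This part of the objection stands, and the figures above are conditional for that reason.

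**Response is undefined, not wrongly defined.** A reader might also infer that response is post-treatment change and that the crossover contrast is thrown away. The article does not say so. It says that subjects act as their own controls, and Data collection and analysis announces comparisons both before versus after and real versus sham. What stands is an ambiguity in the target.

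**The work is exploratory.** The correlation step carries that label, Table 1 lists EEG, MRI and serum measures as exploratory, and the Discussion hedges with a conditional. This lowers the stakes. But the label is attached to the first step rather than to the regression, and it does not correct a biased R-squared.

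**Details may sit in an analysis plan.** That is fair for the adjustment method. It does not cover the choice of screening followed by stepwise selection, which the article states outright.

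**Conclusion.** The concern holds in a conditional form. Screening at least 58 candidates and then running stepwise regression in the same 21 to 24 patients gives optimistic p-values and R-squared under either reading of the multiplicity rule.

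- Without adjustment of the screen, a pure-noise model arises in roughly 67% to 95% of trials per response variable, with mean apparent R-squared about 0.27 to 0.42.
- With adjustment, the chance is about 3% to 5%, but whatever passes is exaggerated and the later stepwise p-values remain invalid.

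The size rests on the count of 58, which is a minimum; on assumed correlations between predictors of 0 to 0.7; on assumed entry and removal criteria of 0.05 and 0.10; and on no candidate being related to response. The ambiguity over the response variable is a separate weakness: it matters only if response means the real phase alone. The point deserves correction because biomarker identification is a prominent aim, but no efficacy conclusion depends on it.

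**What to change.** - Replace screening plus stepwise selection with one penalised regression, for example the lasso. Keep all tuning and selection inside cross-validation or a bootstrap, and report the optimism-corrected R-squared.
- Define the response as the within-patient real-minus-sham difference in MDS-UPDRS-III, adjusted for sequence and period.
- Describe the whole predictor analysis, not only the correlation step, as hypothesis-generating, and bring the Discussion into line.

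The cost is analysis wording and some programming; no patient procedure changes. There are real downsides. Fewer and weaker-looking predictors will be reported. The difference carries measurement error from both periods, so it may be a noisier response. A validated R-squared from 21 to 24 patients will be imprecise and should be reported as such.

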### Blinding

The study will have a double-blind design to improve the reliability of results. Random distribution of participants to groups will be supervised by an external investigator, who will use computer-generated numbers to encode the assignment of patients to intervention groups; thus, neither the neurologist nor the evaluator(s) will know which group a patient is in. The study aims to achieve allocation concealment by recording the patients’ randomized group assignments in sealed envelopes, with the researchers and patients having no control over the random allocations, and ensuring that no one involved in the study is aware of the treatment allocations. After the patient signs the informed consent form, an envelope will be opened, and treatment will be allocated in a coded form. Patients will be randomly allocated into two groups, namely, active iTBS and sham stimulation, in a 1:1 ratio. Group allocation will be communicated via email to the person responsible for applying the iTBS treatment. This person will not take part in the data analysis or in the post-iTBS evaluation. All patients will be naive to TMS, and the patients will be kept blind to their assigned treatments throughout the process.

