### Adherence and dropout

At the start of each stimulation session, the patient will confirm their willingness to participate. The patient will indicate their interest in taking part in our study before each stimulation session, and they will be free to leave at any moment. During the patient’s participation in the study, the research clinician will ensure that the patient is still eligible to participate. An individual will be removed from the study upon losing eligibility or reporting any major negative side effects.

Thus, patients will be asked to drop out of the investigation if any adverse effect occurs after stimulation or if they fail to cooperate to the extent that the normal protocol of the study cannot be carried out. Patients will be free to drop out at any point if they so desire. To improve adherence to the study procedures, telephone follow-up will be carried out during the washout phase so that any adverse consequences can be properly managed. Moreover, if any brain abnormalities are observed during the MRI (e.g., white matter hyperintensities, cerebral vascular lesions, or evidence of space-occupying lesions) or EEG assessments (e.g., epileptiform activity, ictal patterns) or after blood testing (e.g., exaggerated levels of sNfL), the patient will be referred to the proper medical services for further analysis and consideration, which will inform the decision of whether the patient may continue in the study.

Although rescue treatment will not initially be required, nonresponders will have the option to receive another 5 sessions of real iTMS bilaterally over M1 at the end of the study as an add-on rescue treatment. Patients and their relatives will be instructed to maintain their normal daily routines and not to alter their physical exercise patterns, diet, sleep schedules, or any other nonpharmacological treatment throughout the study, as well as to report any change.

Dopaminergic medication for all patients will be stabilized for at least 2 months prior to the study. Patients will need to maintain their dosage of dopaminergic medication until the completion of Phase II. In addition, assessment of nondopaminergic medications will be conducted to determine their influence on the tests performed.

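### Patient deletion and last observation carried forward are poor choices for missing motor scores in this two-period crossover; a likelihood analysis of all observed data is better

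*Protocol article*

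**What the plan says.** The Statistical analysis section of the protocol article makes three statements about missing data.

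- A general intention: "Issues affecting the risk of bias related to missing data in our crossover study will be considered".
- A first rule: "Initially, all patients with missing outcome data will be removed from the analysis of each data subset".
- A further strategy: "Other strategies for managing missing data, such as the last observation carried forward, will also be used to impute values".

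The same section says that patients serve as their own controls. The Procedure and intervention section gives each phase its own baseline and four post-treatment motor evaluations: at the last session, at one week, at two weeks and at 28 days. The phases are separated by a washout of at least three months.

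On expected loss, Recruitment and sample size says that "the total sample size was calculated to be at least 21 subjects", and then: "With an assumed drop-out rate of approximately 20%, we estimated a final minimum sample size of 24 patients". Adherence and dropout adds a withdrawal rule: "patients will be asked to drop out of the investigation if any adverse effect occurs after stimulation".

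**The concern.** The article names two methods, and each has a known weakness in this design.

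**LOCF.** The trial follows motor scores to day 28, and the Discussion calls the persistence of the effect debatable. Carrying an early post-stimulation score to day 28 supplies the answer to that question for the imputed patients. If a score were carried from one phase into the other, a value obtained under one condition would stand in for the other condition.

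**Deletion.** The real-sham contrast is made within patients, so a patient who lacks one phase drops out of it, along with everything observed in the other phase. Withdrawal is tied to adverse effects after stimulation, so loss could depend on the condition received. The patients who remain may then not represent those randomised.

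At stake are a distorted effect estimate and a loss of power in a trial of 24 patients.

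**Working it through.** **Inputs from the protocol article.** 21 evaluable patients for 80% power at two-sided 0.05; 24 enrolled; about 20% drop-out; 1:1 allocation; two phases.

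**Assumed, because the article does not give them.** The effect size is back-solved from 21. The correlation between a patient's two phases is taken as 0.3 to 0.8 (0.5 and 0.7 in simulation).

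**1. The plan's own figures.** The 21 cannot be recomputed without an effect size and SD, so it is taken as given. The step to 24 does not reproduce: 21/(1 - 0.20) = 26.25, so 27, and 24 corresponds to 1 - 21/24 = 12.5% loss. That is a separate issue. What matters here is 24 x 0.80 = 19.2, about 19 complete patients.

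**2. Power of complete cases.** The standardised within-patient effect implied by 21 is (1.960 + 0.842)/√21 = 0.611, or 0.645 using the noncentral t with n - 2 degrees of freedom. With the normal form, power = Φ(0.611√n - 1.960).

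| Complete patients | Normal | t |
|---|---|---|
| 24 | 85.0% | 85.5% |
| 21 | 80.0% | 80.0% |
| 19 | 76.0% | 75.4% |

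**3. LOCF across phases (a scenario, not stated in the article).** Let δ be the true real-sham effect and q = 0.20 the share lost at random before any Phase II post-treatment score.

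- Phase I result carried into Phase II: each such patient's difference is zero, so the estimate is (1 - q)δ = 0.80δ. Simulation gave 0.795 and 0.803.
- Phase II baseline carried, meaning zero change, with a mean sham change of zero: real-first patients keep δ on average and sham-first drop-outs contribute zero. The estimate is [δ + (1 - q)δ]/2 = 0.90δ. Simulation gave 0.895 and 0.893, about 11% attenuation.
- Simulated power under these two forms was about 70-76%.

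**4. LOCF within a phase.** Suppose there is an early effect that has gone by day 28, and the 20% leave during Phase II after an early score, evenly across the two sequences. Only the sham-first half have a real-phase score carried, so 0.20/2 = 10% of the early effect appears at day 28 although none is left. If the effect stays constant to day 28, the mean is not biased.

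**5. Bias of complete cases.** The simulation used 24 patients, one score per phase, 20% losing Phase II, and 3000 runs at each correlation.

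| Loss mechanism (assumed) | Estimate / true effect |
|---|---|
| Completely at random | 0.99 to 1.00 |
| 32% after real, 8% after sham in Phase I, unrelated to score | 1.00 |
| Follows a poor Phase I result | 0.95 to 0.975 |
| Follows a poor response to real stimulation | 1.13 to 1.17 |

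Unequal loss alone did not bias the contrast. Loss linked to the outcome did.

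**6. Keeping the incomplete patients.** A likelihood calculation with known variance used 19 complete patients plus 5 with Phase I only. Power was 79.5%, 78.6%, 77.5% and 77.0% at correlations of 0.3, 0.5, 0.7 and 0.8, against 76.0% for complete cases alone.

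**The case against.** The strongest defence is that the article condenses a fuller plan. It says that bias from missing data will be considered, and it offers LOCF only as an example. The missingness assumption and the ranking of primary and sensitivity analyses are commonly left to an analysis plan, so their absence is no finding. That stands. It does not cover the two methods that the article does name.

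A reader might also infer more than the text supports:

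- **That patients are deleted and the gaps then imputed.** The article presents imputation as an additional strategy, and deletion applies per data subset. A patient lacking one modality is not removed from every analysis.
- **That a missed visit removes a patient from all motor analyses.** If each evaluation were independently missing with probability 2%, 3% or 5%, requiring all ten would leave 82%, 74% or 60% of patients (0.98, 0.97 and 0.95 to the power 10). The article does not define the subset that way. A comparison at one visit needs four values, and the same assumed rates then leave 92%, 89% or 81%.
- **That LOCF crosses the washout.** Nothing says so, and each phase has its own baseline. The 20% figure is therefore an upper scenario. It also cannot apply to the same drop-outs as the within-phase scenario.
- **That drop-out will depend on treatment.** The Safety assessment section reports no significant side effects in existing research, the sham coil is described as similar in sound and sensation, and the withdrawal rule applies to both conditions. The documents support only that loss could depend on treatment.

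Finally, a mixed model recovers little power, and complete cases are essentially unbiased under random loss. Both points are correct and limit the claim.

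**Conclusion.** The point holds in a limited form, as a change that should be made. LOCF is unsuitable here even when loss is random: within a phase it is unbiased for day 28 only if the effect does not change after the last observed visit, and across phases it pulls the contrast towards zero. The attenuation of about 20% or 11% belongs to the cross-phase scenarios with 20% loss before any Phase II post-treatment score, and is not a forecast.

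Deletion at the planned loss leaves about 19 patients against the 21 required, with power of about 75-76%. Its bias is negligible if loss is completely at random. It ranged from 2-5% attenuation to 13-17% overstatement under the two outcome-related mechanisms tried. The withdrawal rule makes such mechanisms plausible but does not establish them. All these sizes rest on the back-solved effect and the assumed correlations and mechanisms.

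**What to change.** In the Statistical analysis section, make the primary motor analysis a likelihood-based mixed model with treatment, period, sequence and visit as fixed effects and patient as a random effect, using every observed visit and phase. It is valid under missing-at-random. Keep complete cases as a sensitivity analysis and delete LOCF. Optionally, add a sensitivity analysis that assigns unfavourable values to patients who withdraw after stimulation, because the mixed model does not fully protect against loss that depends on unobserved scores.

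The cost is slightly more programming and a move away from the simple two-sample test. No visit or procedure changes. The gain in power is modest, from about 75-76% to about 77-79.5%; the main benefits are validity under a weaker assumption and use of partly observed patients.
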